**Secondary Endpoints:**

1. GMT and 4-fold rise rate of anti-omicron neutralizing antibody, 28 days after a single dose of the booster vaccine in adults  $\geq 18$  years of age.
2. GMT of anti-omicron IgG antibody, 4-fold rise rate, GMI, and proportions of neutralizing antibody titered  $\geq 1:16$ ,  $\geq 1:32$  and  $\geq 1:64$  before booster vaccination and 28 days after a single dose of the booster vaccine in adults  $\geq 18$  years of age.
3. GMTs of anti-omicron neutralizing antibody and IgG antibody and the proportions of neutralizing antibody titered  $\geq 1:16$ ,  $\geq 1:32$  and  $\geq 1:64$  in 3 months, 6 months, 9 months and 12 months after full course immunization (i.e., 2 or 3 previous Vero Cell vaccine doses and 1 booster dose).

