**CONFIDENTIAL**

adults  $\geq 18$  years of age.

2. To compare the immune persistence of booster immunization using recombinant COVID-19 vaccine (NVSI-06-09) and inactivated COVID-19 vaccine (Vero cell) in populations  $\geq 18$  years of age.
3. To compare cellular immunity after immunization with NVSI-06-09 vaccine or Vero Cell vaccine in adults  $\geq 18$  years of age.

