#### 4.4 Trial Hypothesis

1. The 4-fold rise rate and GMT (Omicron) of neutralizing antibody of Recombinant COVID-19 Vaccine (NVSI-06-09) after booster vaccination with one dose of vaccine are superior to that of Inactivated COVID-19 Vaccine (Vero cell),  $H_0: \delta \leq 0.0212$  vs.  $H_1: \delta > 0.0212$  (both are a logarithmic scale, equivalent to GMT ratio 95%CI  $> 1.05$ ).
2. After booster vaccination of one dose of Recombinant COVID-19 Vaccine (NVSI-06-09), the 4-fold rise rate and GMT (Omicron) of neutralizing antibody is not inferior to COVID-19 inactivated vaccine (Vero cell), and the non-inferior threshold is  $2/3$  (GMT ratio; the difference on log10 scale is  $-0.176$ ). If the lower bound of GMT ratio 95% CI is  $> 2/3$ , the hypothesis of non-inferiority in post-immunization GMT between experimental group and control group will be concluded.

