**Secondary indicators:**

The antibody GMT (prototype strain) of the experimental group was not inferior to that of the control group 14 days after immunization.

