**Calculating basis for sample size:**

By referring to the relevant data of this product in ex-China clinical trials, 0.55 (logarithmic scale) is taken as the standard difference of the antibody titer of the recombinant COVID-19 vaccine (CHO cell). The probability of type I error  $\alpha=0.025$  (one-sided); power  $1-\beta = 0.9$ ; non-inferiority threshold  $\Delta=-0.17609$  (logarithmic scale, i.e., the lower bound of 95%

CONFIDENTIAL

confidence interval of GMT test group/GMT control group after immunization should be at least 0.67); The test group and the control group are designed according to 1:1.

| Test level (one sided) | Target     | N of each group | Superiority margin         | Actual level of difference between test group and control group | SD          | Total N after considering 20% drop-out |
|------------------------|------------|-----------------|----------------------------|-----------------------------------------------------------------|-------------|----------------------------------------|
| 0.025           | 0.9 | 206      | -0.17609 (2/3 fold) | 0 (1 fold)                                               | 0.55 | 516                             |
| 0.025                  | 0.9        | 262             | -0.17609 (2/3 fold)        | -0.02 (0.95 fold)                                               | 0.55        | 656                                    |
| 0.025                  | 0.9        | 344             | -0.17609 (2/3 fold)        | -0.02 (0.90 fold)                                               | 0.55        | 860                                    |
| 0.025                  | 0.9        | 566             | -0.17609 (2/3 fold)        | -0.07 (0.85 fold)                                               | 0.55        | 1416                                   |

Based on the above considerations and the drop-out rate, it is planned to enroll 516 participants.

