#### **10.6 Multiplicity**

Not applicable.

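### Section 10.6 sets multiplicity aside, yet two hypotheses are each powered at full one-sided 0.025 with no stated order, and 28 secondary comparisons carry no descriptive label

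*Protocol*

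**What the plan says.** Section 10.6 of the protocol disposes of multiplicity with "Not applicable" and gives no reason.

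Section 10.1 contains two sample size calculations, each at one-sided alpha 0.025 and 90% power:

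- Primary: superiority of the Omicron GMT at day 14, with a margin of 0.0212 on the log scale (ratio 1.05).
- Secondary: "The antibody GMT (prototype strain) of the experimental group was not inferior to that of the control group 14 days after immunization", with a margin of -0.17609 on the log scale (ratio 2/3). This row gives the planned enrolment of 516.

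Section 4.4 states a superiority and a non-inferiority hypothesis. The superiority hypothesis says that the 4-fold rise rate and GMT "after booster vaccination with one dose of vaccine are superior to that of Inactivated COVID-19 Vaccine (Vero cell" vaccine. Neither hypothesis names a day. The non-inferiority hypothesis names Omicron, not the prototype strain, and says that non-inferiority is concluded when the lower 95% confidence bound of the GMT ratio exceeds 2/3.

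The secondary objectives in section 3.2 are worded as comparisons of the two vaccines. The secondary endpoints in section 4.3 cover day 28 and then, at 3, 6, 9 and 12 months, "GMTs of anti-omicron neutralizing antibody and IgG antibody and the proportions of neutralizing antibody titered" at or above 1:16, 1:32 and 1:64. Section 10.3.3 provides a between-group 95% confidence interval for post-vaccination GMTs only, and does not limit it to day 14.

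**The concern.** Two separately powered hypotheses, each with its own margin and full alpha, raise a multiplicity question unless one is nested in the other or an order is fixed. The protocol gives no order, and its two statements of the non-inferiority hypothesis disagree on the strain, which decides whether the question arises at all. As written, prototype-strain non-inferiority could be claimed at full alpha even if Omicron superiority failed.

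Behind these stand 28 secondary comparisons. They are neither called descriptive nor tied to the primary result, and only the exploratory endpoints carry a non-confirmatory label. If their intervals were read as findings, no stated error rate would cover them.

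**Working it through.** **1. The plan's own figure.** Inputs from the secondary calculation in 10.1: alpha 0.025 one-sided, power 0.90, SD 0.55, margin 0.17609, true difference 0, allocation 1:1, drop-out 20%.

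n per group = 2 × SD² × (z₀.₉₇₅ + z₀.₉₀)² / margin² = 0.605 × 10.507 / 0.17609² = 205.01, rounded up to 206.

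With drop-out: 206 / 0.8 = 257.5, so 258 per group and 516 in total. The plan's 206 and 516 reproduce, and the trial is sized on the secondary test.

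**2. The two powered hypotheses, if the strains differ.** Take both nulls as true and the two test statistics as normal with correlation ρ. The protocol gives no correlation, so ρ is an assumption. Under independence the chance of at least one false claim is 1 − 0.975² = 0.049.

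| ρ | 0 | 0.5 | 0.9 |
|---|---|---|---|
| At least one false claim | 0.049 | 0.045 | 0.035 |

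**3. The same pair, if non-inferiority is on Omicron at day 14.** A lower bound above 1.05 is also above 2/3.

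- If the true ratio is at or below 2/3, any false superiority claim is also a false non-inferiority claim, so the total error is at most 0.025.
- If the true ratio lies between 2/3 and 1.05, only the superiority claim can be false, again with probability at most 0.025.

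Testing both therefore costs no alpha.

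**4. Counting the secondary comparisons (4.3).**

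- Day 28: neutralising GMT and 4-fold rise (2); IgG GMT, 4-fold rise and GMI (3); three titre thresholds (3). Total 8.
- Persistence: (2 GMTs + 3 thresholds) × 4 time points = 20.
- All: 8 + 20 = 28.

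Of these, 2 GMTs × 5 time points = 10 have a between-group interval under 10.3.3. The other 18 (15 threshold proportions, 2 four-fold-rise rates, 1 GMI) have no stated between-group method.

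**5. Error rate if the 28 were read as claims.** With all nulls true, one-sided 0.025, equal correlation ρ and z = 1.96:

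FWER = 1 − ∫ φ(u) · Φ((z − √ρ·u) / √(1−ρ))ᵏ du

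| ρ | 0 | 0.3 | 0.5 | 0.7 | 0.9 |
|---|---|---|---|---|---|
| k = 28 | 0.508 | 0.338 | 0.247 | 0.165 | 0.085 |
| k = 10 (GMTs) | 0.224 | 0.178 | 0.144 | 0.107 | 0.064 |

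**6. Cost of gating.** With 206 evaluable per group and SD 0.55, the standard error is 0.55 × √(2/206) = 0.0542.

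- Superiority: (0.200 − 0.0212) / 0.0542 = 3.30, power Φ(3.30 − 1.96) = 0.91.
- Non-inferiority: 0.17609 / 0.0542 = 3.25, power 0.90.
- Both: 0.91 × 0.90 = 0.82 if independent; 0.88 at ρ = 0.9 (bivariate normal).

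**The case against.** Labelling and ordering secondary endpoints is commonly left to a statistical analysis plan, which is not shown here. The 28 comparisons have no null, margin, alpha or success rule, and an objective worded as a comparison is not a confirmatory claim. Most of this stands: the 29-test family (the 28 plus the prototype-strain test) is not one that the protocol declares. What does not stand is silence as a defence. Section 10.6 is not silent; it states that the matter does not arise, so an ordering placed in a later plan would contradict it.

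Three stronger readings are tempting, and the documents do not support them.

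- A reader might infer that at least one false secondary claim is likely. The risk passes one half only with independence and every null true. The endpoints are plainly dependent: three thresholds are cut from one titre, rise rates and GMI come from paired data, and the same people are measured repeatedly. The design itself expects an Omicron ratio of 1.6.
- A reader might infer that any interval excluding the null may be reported as a demonstrated advantage. No rule in the protocol says so.
- A reader might infer that the 4.4 hypotheses extend to day 28 because they name no day. The primary objective, the primary endpoint and both sample size statements all say day 14, so this is a drafting gap.

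It is also fair to object that the inflation for the pair depends on the strain. Section 4.4 names Omicron, 4.3 lists no prototype-strain endpoint, and the objectives in 3.1 and 3.2 use a phrase that joins prototype and Omicron. If Omicron is meant, the inflation disappears.

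**Conclusion.** The point holds in a limited form. The entry in 10.6 does not fit a protocol that powers two hypotheses at full one-sided 0.025 without an order. If non-inferiority concerns the prototype strain, as 10.1 says, the chance of at least one false claim with both nulls true is 0.035 to 0.049, or 1.4 to 2.0 times the stated 0.025, for assumed correlations of 0.9 to 0. If it concerns Omicron at the same time point, as 4.4 says, there is no inflation. The documents do not settle which applies.

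The 28 secondary comparisons are an unlabelled family, not a set of declared claims. Read as claims, they would carry a one-sided family-wise error of about 8.5% to 51%, or 6% to 22% for the 10 GMT contrasts with a stated interval. Both ranges assume that all nulls are true and equal correlations of 0.9 to 0. The primary test at its own alpha and the total of 516 are unaffected.

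**What to change.** 1. Reconcile the strain of the non-inferiority hypothesis between 4.4 and 10.1, and state day 14 in both 4.4 hypotheses.
2. Replace the entry in 10.6 with a fixed sequence, each step at one-sided 0.025 and tested only if the step before succeeds: day-14 Omicron GMT superiority; then day-14 prototype-strain GMT non-inferiority; then, if a claim is wanted, day-28 Omicron GMT superiority. If non-inferiority is on Omicron, test it first and superiority second, at no alpha cost.
3. State that all other secondary endpoints are descriptive: estimates with nominal 95% confidence intervals and no formal claim.

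This changes wording only, with no added participants or samples and no alpha taken from the primary test. It should be settled before unblinding, since an order chosen afterwards gives no protection. There are two costs. The chance of reaching and passing the gated prototype-strain test is about 0.82 (independent) to 0.88 (correlation 0.9) instead of 0.90, at 206 evaluable per group, SD 0.55 and the true differences assumed in 10.1. Formal claims on the remaining secondary endpoints are also given up.

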**Exploratory Endpoints**

1. The efficacy of NVSI-06-09 vaccine against omicron-caused COVID-19, especially severe cases (including deaths), 14 days after booster vaccination in adults  $\geq 18$  years of age.
2. Cross-protecting effect of neutralizing antibodies against different variants (Alpha, Beta, Delta, and Omicron), 14 days after a single dose of the booster vaccine in adults  $\geq 18$

**CONFIDENTIAL**

years of age.

3. Cross-protecting effect of neutralizing antibodies against different variants (Alpha, Beta, Delta, and Omicron ), 28 days after a single dose of the booster vaccine in adults  $\geq 18$  years of age.

#### 4.4 Trial Hypothesis

1. The 4-fold rise rate and GMT (Omicron) of neutralizing antibody of Recombinant COVID-19 Vaccine (NVSI-06-09) after booster vaccination with one dose of vaccine are superior to that of Inactivated COVID-19 Vaccine (Vero cell),  $H_0: \delta \leq 0.0212$  vs.  $H_1: \delta > 0.0212$  (both are a logarithmic scale, equivalent to GMT ratio 95%CI  $> 1.05$ ).
2. After booster vaccination of one dose of Recombinant COVID-19 Vaccine (NVSI-06-09), the 4-fold rise rate and GMT (Omicron) of neutralizing antibody is not inferior to COVID-19 inactivated vaccine (Vero cell), and the non-inferior threshold is  $2/3$  (GMT ratio; the difference on log10 scale is  $-0.176$ ). If the lower bound of GMT ratio 95% CI is  $> 2/3$ , the hypothesis of non-inferiority in post-immunization GMT between experimental group and control group will be concluded.

#### 4.5 Safety Observation Indicators and Grading Criteria

##### 4.5.1 Safety Observation Indicators

###### (1) Adverse events collected in 0-7 days

**Local adverse events:** pain, induration, swelling, rash, redness and pruritis.

**Systemic adverse events:** fever, diarrhoea, constipation, dysphagia, anorexia, vomiting, nausea, myalgia (systemic), arthralgia, headache, cough, dyspnoea, systemic pruritis (no skin damage), abnormal skin mucosa, acute allergic reactions, tiredness/fatigue, and dizziness

**Other adverse events:** any medical events other than the above mentioned during clinical studies, such as acute diseases, accidental injuries, etc.

###### (2) Adverse events collected in 8-28 days

**CONFIDENTIAL**

Any medical events, such as acute diseases and accidental injuries occurred during 8~28 days in clinical studies.

### **(3) Pregnancy events**

Collect all pregnancy events and outcomes between vaccination and the end of the study (6 months after a full course of immunization). Follow-up of the newborns should last at least 1 month after birth.

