### **5.1 Participant Population**

#### **5.1.1 Inclusion Criteria**

Individuals are eligible to participate in this study if all of the following criteria apply:

- Age:  $\geq 18$  years;
- Judged by the investigator that the health condition is well after inquiry and physical examination;
- Vaccinated with 2 or 3 doses of inactivated COVID-19 vaccine (Vero Cell vaccine)  $\geq 6$  months prior to study screening and according to product insert;
- Female participants who are not pregnant or nursing or at the time of enrolment (confirmed via negative urine pregnancy test), and do not have plans to become pregnant within the first 6 months after enrollment. Effective contraceptive measures have been taken within 2 weeks before study inclusion and initiation;
- Be able and willing to provide written informed consent to participate in the study and complete all study requirements according to the study protocol.

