**CONFIDENTIAL**

respectively, the participants were followed-up by telephone and guided to observe the adverse events correctly and fill in the diary card.

3. On the 14th day after vaccination, the investigator reviews the filling of the diary card during this period and re-collect the diary card.
4. On the 8th -28th day after vaccination, the investigator uses telephone follow-up once a week, combined with an active report of the participants to monitor the safety.
5. When it is known that the participant has adverse reactions/events of Grade 3 or above, a face-to-face visit should take place within 24 hours.
6. SAEs and AESIs are observed from the first dose to 12 months after the full course of vaccination via monthly telephone follow-up calls and self-reports from the participants.
7. Participants should contact the doctors on informed consent form/diary card immediately if developed any COVID-19 like symptoms.

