## 7.9 Study Duration

Early Participant Recruitment: 1 month;

Booster Vaccination + immune persistence observation: about 13 months

Sample Testing: approximately 1 month

Complete the Summary Report: about 1 month

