## 7.10 Site Close

All participants completed long-term safety observation for 12 months after vaccination and blood collection for 12 months after immunization. Trial sites will be closed and immune persistence evaluation will be initiated only once the following activities have been completed:

1. Completed all study requirements according to the study protocol
2. Locked the database
3. Clarification of data by the statistician (blind audit)
4. Unblinded the necessary study staff to evaluate the safety, immunogenicity and

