### **8.3 Handling and Reporting of Serious Adverse Events**

Serious adverse events refer to adverse medical events such as disability or loss of function, the need for hospitalization or prolonged hospitalization of participants, and congenital abnormalities or birth defects.

Monitoring and reporting of adverse events in vaccine clinical trials are jointly completed by participants, serious adverse event investigators, trial sites and responsible institutions at different observation time points with different stages.

The Sponsor is the main body responsible for monitoring, evaluating and SAE reporting safety information of vaccine clinical trials. Designated person acts as the administrator for clinical trial safety information monitoring and SAE reporting, and work with investigators to establish SOPs for clinical trial safety information monitoring and SAE reporting, know well the latest status of the safety information of the whole clinical trial, and timely report updates to all clinical trial institutions/ investigators and regulatory authorities.

If it is difficult to make a judgment on the correlation between SAE and vaccine or there is doubt about the judgment, when it is necessary to make a new judgment, the expert meeting shall make a judgment after argumentation.

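### Pregnancy collection is tied to a 6-month end of study in a trial that runs 12 months, leaving pregnancies first arising in months 6-12 ambiguous and conflicting with the newborn follow-up rule beside it

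*Protocol*

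**What the plan says.** The pregnancy rule is in Protocol section 4.5.1, item (3): "Collect all pregnancy events and outcomes between vaccination and the end of the study (6 months after a full course of immunization". The sentence after it adds: "Follow-up of the newborns should last at least 1 month after birth".

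The secondary endpoints in section 4.3 spell out what a full course means: "full course immunization (i.e., 2 or 3 previous Vero Cell vaccine doses and 1 booster dose". The course is therefore complete on the day of the booster, and the parenthesis in 4.5.1 means 6 months after the booster.

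Other sections set the length of the study differently:

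- Section 7.3.1, item 6: "SAEs and AESIs are observed from the first dose to 12 months after the full course of vaccination via monthly telephone follow-up calls". Primary endpoint 5 in section 4.3 and the AESI text in section 4.5.4 give the same 12 months.
- The Schedule of Events places the last visit, V13, at 12 months.
- Section 7.9: "Booster Vaccination + immune persistence observation: about 13 months".
- Section 7.10, as the condition for closing sites: "All participants completed long-term safety observation for 12 months after vaccination and blood collection for 12 months after immunization".

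Two further provisions bear on the point. The inclusion criteria (section 5.1.1) require that women "do not have plans to become pregnant within the first 6 months after enrollment". The definition of a serious adverse event in section 8.3 includes "congenital abnormalities or birth defects".

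**The concern.** No other section supports a study end at 6 months. The rule in 4.5.1 (3) is one that sites carry out themselves, so a wrong end date bears directly on what is recorded. Two things are at stake.

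First, a site that reads the parenthesis literally would stop recording new pregnancies at about D180, while a site that reads the words before it would go on to about D360. Whether a pregnancy first reported in month 8 enters the database would then depend on the site's reading.

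Second, the rule applies the same limit to outcomes as to events. A pregnancy that begins after the booster cannot reach term within 6 months of it, so a 6-month limit on outcomes cannot be squared with the newborn follow-up required in the next sentence.

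**Working it through.** No sample-size or power figure is involved. The check is a comparison of passages followed by day arithmetic.

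**Inputs from the protocol**

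- 6 months = D180 and 12 months = D360, each with a window of +30 days (section 7.4, Blood Sample Numbering Rule).
- Pregnancy test negative within 24 hours before vaccination (Schedule of Events, footnote 2).
- Newborn follow-up of at least one month, taken as 30 days.

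**Assumptions (the protocol gives no figures)**

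- Term gestation of 37, 40 or 42 weeks, counted from the last menstrual period, with conception 2 weeks after that.
- Conception between day -14 (too recent for the entry test to detect) and day 180.

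**Step 1. Months left uncovered on the literal reading.** 360 - 180 = 180 days, and 180/360 = one half of the 12-month follow-up.

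**Step 2. When a term birth falls.** Birth day = conception day + (gestation weeks - 2) x 7. The newborn check ends 30 days later.

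| Conception day | 37 weeks: birth / check ends | 40 weeks: birth / check ends | 42 weeks: birth / check ends |
|---|---|---|---|
| -14 | 231 / 261 | 252 / 282 | 266 / 296 |
| 0 | 245 / 275 | 266 / 296 | 280 / 310 |
| 180 | 425 / 455 | 446 / 476 | 460 / 490 |

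Even the earliest case, D231, is later than D180 and later than D180 + 30 = D210. A term birth by D180 would need conception by day 180 - 245 = -65 at 37 weeks, or 180 - 280 = -100 at 42 weeks. The entry test is meant to exclude such pregnancies.

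**Step 3. What the newborn sentence requires.** For conceptions from day -14 to day 0, the newborn check ends between D261 and D310. It can be met only by following a pregnancy past D180 to delivery and for a month beyond. The two sentences of 4.5.1 (3) therefore conflict if the 6-month limit applies to outcomes.

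**Step 4. Is changing 6 months to 12 enough?** Pregnancies arising in D180-D360 would then be collected. Not every birth would fall inside the window. The latest conception day with a term birth by D360 is 360 - (gestation weeks - 2) x 7, which gives day 115 (37 weeks), 94 (40 weeks) or 80 (42 weeks). For the newborn check also to end by D360, the days are 85, 64 and 50. Later conceptions deliver, or finish the check, after the last scheduled visit. The new date therefore needs an explicit statement that follow-up of a reported pregnancy continues past it.

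**The case against.** The strongest reply is that little is lost in practice. The newborn sentence has no 6-month cap. The natural way to read the two sentences together is that the first sets which pregnancies are picked up and the second sets how long they are followed. Birth defects are also serious adverse events, observed to 12 months. And if the words before the parenthesis govern, nothing in months 6-12 is uncovered.

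Most of this stands. A reader might infer from the 6-month limit that no term birth and no birth defect after a post-booster pregnancy would ever be recorded. The protocol does not support that: the newborn rule carries identified pregnancies through delivery, and the serious adverse event route is a second way in. A reader might also infer that collection stops just when pregnancies become likely, because the entry restriction lapses at 6 months. The protocol gives no pregnancy rate before or after that point, so this remains conjecture.

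The reply does not remove the contradiction. A sensible reading is still only one of two, and sites may choose differently. The serious adverse event route is a partial backstop. It lists congenital abnormality but not pregnancy or normal birth, so on its own it would give abnormal cases without the pregnancies they came from. It also ends at 12 months, before term delivery for conceptions after about day 80-115.

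**Conclusion.** The point holds as an internal inconsistency in a safety-collection rule. The protocol ends the study at 6 months in one place and at 12 months or more everywhere else. On the literal reading, pregnancies first arising in D180-D360, half of follow-up, fall outside collection; on the other reading they are inside. The 6-month limit on outcomes also conflicts with the newborn follow-up in the same item, since term birth after conception on the booster day falls at about D245-D280.

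The half-of-follow-up figure depends on the parenthesis prevailing, and the birth dates depend on the assumed gestation of 37-42 weeks. The number of women affected cannot be estimated from the protocol. Pregnancy is not a listed endpoint, and neither sample size, power nor the primary immunogenicity analysis is touched. Severity is minor.

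**What to change.** Reconcile section 4.5.1 (3) with the study end used elsewhere:

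1. Replace the 6-month parenthesis with 12 months after the booster.
2. State that any pregnancy reported by then is followed to its outcome and through the newborn follow-up already required, even when that runs past the last visit.

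The second statement is needed because, as step 4 of the working shows, the date change alone would leave births from later conceptions outside the window.

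The cost is a short text correction. Section 7.3.1 already provides monthly calls to 12 months, and the Schedule of Events already has visits at 9 and 12 months, so reporting needs no new contacts up to then. The one downside is that a few ongoing pregnancies must be followed after the 12-month visit: under the assumptions above, to about D455-D490 for a conception on day 180, and later for later conceptions.
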